### Procedure

One member of the study team has already visited the selected schools and informally discussed the research with the school administrators. All the selected schools agreed to participate in the study, and the school head teachers provided support for the study. During the subsequent visit to the schools, formal study introduction letters and supporting documents will be provided to the school administrators. The research team members will then explain pertinent study details to the school authorities.

Informed consent will be sought from the teachers before they participate in the study. The relevant details pertaining to the study, including the purpose and significance of the study and ethical concerns including privacy, confidentiality, legal rights, and informed consent, etc., will be explained in detail to the selected participants in English. The research team will also respond to any identified participants’ concerns in relation to the proposed study.

Informed consent from parents and assent from students will be obtained before the students are enrolled in the study. Selected students will be given a parental consent document that they will take home to their parents to sign or thumb-print. The consent document written in English and Runyankole will provide the parents with relevant information about the study including the ethics involved in the study. After obtaining parental consent, the students will assent before they are formally enrolled in the study.

Students in Uganda use English as the medium of instruction throughout the educational cycle. Therefore, the study questionnaire will be administered in English. A pilot study was conducted at one coeducational secondary school in Mbarara district. The pilot test verified the practicality of the data collection procedure and assessed the ease of use of the research instrument.

During the data collection period, the research team will closely supervise the students as they fill in the questionnaire. Research team members will each administer and supervise small groups of about three to five students each as they complete the questionnaire. Previous studies in Africa indicated that children and adolescents provide accurate and reliable information during research [21, 23, 32].

A set of questionnaires will be administered to the teachers, too. The research team will be available during the data collection period and will oversee the completion of the questionnaire. Additionally, in case of any clarification or request for more information, the research team will be available to attend to any concerns raised by the selected study participants.

### Intervention

ICC-T intervention is a training workshop, which lasts for 5.5 days, for teachers, with 8 hours spent in training on each full day. ICC-T aims at improving teacher-student relationships, changing teachers’ attitudes and behaviors concerning the use of violent disciplinary measures, and preventing harsh and violent discipline in the school setting. The ICC-T core ideas are based on the childcare guidelines of the American Academy of Pediatrics [41].

ICC-T follows core tenets, including incorporating a participative method in which the teachers are encouraged to take an active role during the workshop. Theory and practice are combined during the workshops to enable the teachers to integrate the attained ICC-T skills into the daily work routine at school. During the workshop, confidentiality is emphasized to enable the teachers to freely speak about their work-related tribulations, their desires, and experiences with violent discipline in a trusting and welcoming environment. ICC-T’s sustainability is achieved through rigorous rehearsal of previously learned material, teambuilding events, support supervision, peer consultation, formation of referral networks, and personal reflection on personal behavior. ICC-T ensures that the acquired skills and knowledge will be integrated into the teacher’s everyday school endeavors. Likewise, sustainability is achieved through provision of feedback during the course of the training and through case discussions.

ICC-T is based on five essential components that foster better student-teacher relations and a reduction in school physical punishment. ICC-T training has sessions on teacher-student interactions, maltreatment prevention, effective discipline strategies, identifying and supporting burdened students, and practical implementation of ICC-T aspects in the school setting.

Sessions on teacher-student interactions include topics such as communication skills, instructions and expectations, teachers as role-models, and rules in the classroom. These sessions assist teachers in understanding students’ behavior and highlight teachers’ responsibility as role models for the students. The sessions aim at improving teacher-student relations.

Maltreatment prevention sessions discuss the undesirable outcomes of violent disciplinary measures. Teachers use self-reflection to make a connection between their own childhood experiences of violent punishment, their current use of violent punishment, and its consequences. Discussion topics in this session consist of frequent disciplinary methods, myths about the utility of violent punishment, consequences of violent disciplinary methods, and alternative discipline approaches.

Session on effective discipline strategies intend to equip teachers with non-violent alternatives. Through role-plays teachers will learn how to use non-violent strategies practically, such as privilege removal and reinforcement, to foster desired behavior.

Teachers need to effectively recognize and assist troubled students. This task requires teachers to acknowledge that students may suffer from emotional and behavioral problems. This session will discuss the common internalizing and externalizing behavior problems, developmental delays, and student stress. Afterwards, diverse methods of assisting distressed students will be discussed.

Sessions on ICC-T implementation aim for integrating the learned material into the daily work routine in the school setting. Successful implementation includes collaboration with school staff and peer consultation.

The proposed training strategies include presentations, discussions, question and answer sessions, and supervised practical sessions. The training will be based on the previous success of ICC-T intervention training for teachers in Tanzania. The training was feasible, and first evidence of its effectiveness was found, e.g., a change in teachers’ positive attitudes towards emotional and physical violence and the use of and exposure to physical and emotional violence reported by students and teachers [30, 31].

### Control

At the randomly selected control schools no intervention will be implemented. However, the study will control for the potential influence of other workshops for teachers that may take place during the course of the study. The school administrations will provide information on all such programs during the course of the study.

### Outcome measures

Our study intends to test the effects of ICC-T training on the use of violence by teachers at school. This primary outcome measure is assessed by students’ self-reported experiences of violence (emotional and physical violence) as well as teachers’ self-reported use of violence (emotional and physical violence). Secondary outcome measures include teachers’ attitudes towards violence (emotional and physical violence) as well as student’s mental health (see Fig. 2).

All measures selected for the trial have been used in previous studies in East Africa. Further, the reliability coefficients of the instruments in those studies were acceptable [21, 23–25, 30–32, 37, 38].

#### Students

##### Exposure to physical and emotional violence

The Conflict Tactics Scale (CTS) will assess exposure to common disciplinary measures at school from the students’ perspective. The original CTS assesses diverse disciplinary behaviors including physical assault, emotional and psychological aggression, neglect, and non-violent discipline. For the current trial a modified version of the CTS [30, 37, 38] that has been used in previous studies in Tanzania will be implemented. It measures physical violence with 13 items and emotional violence with five items. Items are rated on a 7-point Likert scale from “never” scored as 0 to “more than 20 times” scored as 6. Subscale scores are derived by summing up the item scores. Physical violence scores range from 0 to 78, while the emotional violence scores range from 0 to 30. The scale has acceptable internal consistency for physical violence (α = .55) and emotional violence (α = .69) in previous studies. The scale reliabilities are acceptable, as the scales assess situations where the items measure relatively exceptional incidents [1].

##### Mental health problems

The Strengths and Difficulties Questionnaire (SDQ) will measure the students’ behavioral problems, namely internalizing and externalizing problems. The 25-item SDQ assesses four problem behaviors: emotional problems, peer problems, conduct problems, and hyperactivity. Each subscale has five items rated on a scale ranging from “not true” (0) to “certainly true” (2). Reversed items are recorded before the computation of the total scale score (sum of scores for hyperactivity, emotional symptoms, conduct problems, and peer problems) that ranges between 0 and 40, with a score above 20 representing the presence of mental health problems. The Cronbach alpha reliability of the total difficult score was .82 [42]. Internalizing problems including peer problems and emotional symptoms had Cronbach’s alpha coefficients of .61 and .75, respectively. Internal reliabilities for externalizing problems were .72 for conduct problems and .69 for hyperactivity in the pilot validation study [42].

#### Teachers

##### Purpose-built measures for ICC-T training evaluation

The purpose-built measures adapted from Kaltenbach et al. [31] and Nkuba et al. [30] will be used to assess the feasibility of ICC-T in the cultural context of southwestern Uganda. We follow the guidelines for feasibility studies by Bowen et al. [43] in assessing the demand, applicability, acceptability, and integration of ICC-T core elements in the teachers’ daily work. The demands will be assessed through examination of teachers’ positive attitudes towards violent disciplining before and directly after training. The applicability of the training (e.g., expectations about the workshop, relevance of the workshop) will be measured before the intervention, directly after the intervention, and at the follow-up assessment. Furthermore, we will examine the acceptability of the training (e.g., satisfaction with the training, evaluation of new knowledge) directly after the intervention and at the follow-up assessment. Finally, we will assess the integration of the ICC-T core elements in teachers’ daily work at school directly after the intervention and at the follow-up assessment.

As measures of efficacy we will assess the change in attitudes towards and use of violent disciplinary measures as well as a perceived change in the teacher-student relations (e.g., How did the training influence your understanding of students?). After a 3 months follow-up, integration and implementation of learned ICC-T material into daily work routines will be measured. Attitudes towards emotional and physical violence and actual application of violent discipline strategies in the school will be assessed using items from the modified CTS that have been used previously in Tanzanian studies [30, 31, 37, 38]. Teachers will respond to the 18 items (13 items measure physical violence, and 5 items measure emotional violence) of the CTS with regard to the use of school violence. The CTS items are scored using a 7-point answer category from “never” scored as 0 to “more than 20 times” scored as 6. Subscale scores are derived by summing up the item scores. Physical violence scores range from 0 to 78, while the emotional violence scores range from 0 to 30.

Moreover, teachers will be asked to report their attitudes towards violent discipline strategies using the 18-item modified CTS. The items are scored on a 4-point Likert scale from “never OK” scored as 0 to “always or almost always OK” scored as 4. Subscale items are summed up to yield scores for physical violence (range 0–52) and emotional violence (range 0–20).

### Analysis

Primary analysis will be carried out based upon the groups as randomized (“intention to treat”). We will use the last-observation-carried-forward approach; i.e., in drop-outs we assume no change from pre-assessment to follow-up. Results will be presented including appropriate effects sizes and a measure of precision (95% confidence intervals).

Our main analysis of the primary outcomes, students’ exposure to and teachers’ use of physical and emotional violence, will be *time × group* interaction effects using repeated multivariate analysis of variance (MANOVA). In case of a noted cluster effect (intra-cluster correlation coefficient > .10) we shall use multilevel analysis. Multivariate interaction effects and the univariate interaction effect of each outcome variable will be tested first. Paired *t* test analysis will examine the differences from the pre-assessment to follow-up assessment in the intervention group while the independent *t* test will examine whether there is a difference between the control group and intervention group at the follow-up assessment. Effect sizes η^2^ ≥ 0.01, η^2^ ≥ .0.06, and η^2^ ≥ 0.14 will be considered to represent small, moderate, and large effect sizes correspondingly. For *t* tests effect size interpretation will be guided by the suggestion of Cohen where *d* ≥ 0.20, *d* ≥ 0.50, and *d* ≥ 0.80 will represent small, medium, and large effect sizes, respectively.

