### Consequences of violence by teachers at school

School violence is a painful experience associated with physical injuries [20, 21], child aggression and antisocial behavior [22], externalizing and internalizing behavioral problems [4], and depression and post-traumatic stress disorder (PTSD) symptoms [23–25]. Research findings also emphasize that students who have been victims of violence at school showed lower self-esteem, engaged in destructive avoidance behavior, and limited their communication strategies in the school locale [14]. In accepting violence as the normative disciplinary measure, students do not understand that the use of violent disciplinary measures is a violation of their rights [20].

Furthermore, the use of violence in the school leads to chronic fear of violent teachers as well as school avoidance [14]. Consistently, violence by teachers at school has resulted in negative education outcomes, such as low education achievement and school absence [21], poor academic performance, and increased school drop-out rates and absenteeism [18, 20].

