### Participants

Due to the longitudinal nature of the study which necessitates two data collection points, the focus of this study is on students in the 8th and 9th years of formal schooling. Based on a previous study that used a similar design to test the efficacy of ICC-T in Tanzania [30], we would expect a moderate to large effect on students’ self-reported exposure to violence. An a priori power analysis (α = .05, power = 0.80, moderate effect size of ƒ = 0.25) using G*Power software [40] indicated a required total sample size of at least *n* = 128 students to detect significant interaction effects. To adjust for the nested design of the study, we calculated the following design effect (DE): DE = 1 + (fixed cluster size considering drop-outs − 1) × intra-cluster correlation coefficient. Considering 60 students per school, a drop-out rate of 20%, and an intra-cluster correlation coefficient of 0.05, the DE for the student sample is 3.35, which results in a required sample size of at least 430 students. We aim to randomly select, at each school, 30 students from Senior One (8th year) and 30 from Senior Two (9th year). The target sample will thus be 720 students in the age range between 12 and 17 years. At the classroom level a list of all students will be obtained from the school administration. Stratified random sampling will be used to select 15 boys and 15 girls from each class or stream.

All teachers who are officially working in the selected schools will be included in the study sample. Based on the previous study in Tanzania [30], we would expect a large effect on teachers’ self-reported use of violence against students. An a priori power analysis (α = .05, power = 0.80, moderate to large effect size of ƒ = 0.35) using G*Power software [40] indicated a required total sample size of at least *n* = 67 teachers to detect significant interaction effects. To adjust for the nested design of the study, we again calculated the DE. Considering a minimum of 15 teachers per school, a drop-out rate of 20%, and an intra-cluster correlation coefficient of 0.05, the DE for the teacher sample is 1.55, which results in a required sample size of at least 104 teachers. Our target sample will be at least 15 teachers per school, resulting in a total sample of at least 180 teachers.

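### The primary missing-data rule (last observation carried forward) gives every drop-out a change of zero, which can bias the time × group estimate in either direction and leaves its 95% interval covering too seldom

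*Protocol article*

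**What the plan says.** Under Analysis, the protocol article ties the intention-to-treat primary analysis to one missing-data rule: "We will use the last-observation-carried-forward approach; i.e., in drop-outs we assume no change from pre-assessment to follow-up". No other rule is named. The main test of the primary outcomes (students' exposure to violence and teachers' use of it, physical and emotional) is of time × group "interaction effects using repeated multivariate analysis of variance (MANOVA"), with multilevel analysis if the intra-cluster correlation exceeds .10. Effect sizes and 95% confidence intervals are promised.

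Under Participants, the student sample size rests on "power = 0.80, moderate effect size of ƒ = 0.25" and needs "128 students to detect significant interaction effects". It is then inflated: "Considering 60 students per school, a drop-out rate of 20%, and an intra-cluster correlation coefficient of 0.05", so that "the DE for the student sample is 3.35, which results in a required sample size of at least 430 students". The planned samples are larger: 720 students and at least 180 teachers in 12 schools. The 20% enters only through the cluster size in the design effect. The assumed effect is not reduced for participants who will be given zero change.

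The Discussion expects teachers to be lost through retirement, transfer and resignation, and students through leaving school or moving to another school.

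**The concern.** With one baseline and one follow-up, carrying forward is the same as setting a drop-out's change score to zero. At the expected rate this affects 0.20 × 720 = 144 students and 0.20 × 180 = 36 teachers. The time × group interaction with two time points is a comparison of mean change between arms, so these zeros enter the primary estimate as if they had been measured.

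A teacher's transfer or a student's move says nothing about whether violence stayed the same, so the assumption has no support in the document. At stake are the size of the reported effect, the meaning of its confidence interval and, if drop-out differs between arms, the false-positive rate. All primary outcomes are affected.

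**Working it through.** **Inputs from the protocol article.** Two assessments; 12 schools, six per arm; 60 students and at least 15 teachers per school; 20% drop-out; intra-cluster correlation 0.05; f = 0.25 for students (d = 2f = 0.50) and f = 0.35 for teachers (d = 0.70).

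**Assumptions.** The effect size is on the scale of the change score (SD 1). Drop-out is unrelated to outcome within an arm. Arm-specific drop-out rates and a common trend are illustrative, because the documents give none.

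**1. The plan's own figures.** An F test with 1 numerator df and noncentrality N·f² needs N = 128 for f = 0.25 (power 0.801) and N = 67 for f = 0.35 (power 0.806). The design effects are 1 + (48 − 1) × 0.05 = 3.35 and 1 + (12 − 1) × 0.05 = 1.55. Then 128 × 3.35 = 428.8 (stated 430) and 67 × 1.55 = 103.85 (stated 104). Both are reproduced. The power of 0.80 belongs to these minimum sizes.

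**2. Expected estimate under the rule.** Let δ be the true effect on change, τ the change common to both arms, and p_I, p_C the drop-out proportions:

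E = (1 − p_I)(τ + δ) − (1 − p_C)τ.

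With p_I = p_C = 0.20, E = 0.8δ. For students 0.50 becomes 0.40; for teachers 0.70 becomes 0.56.

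**3. Interval, equal drop-out.** Simulation of 12 schools with a school-level t test on 10 df and no change in controls:

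| | Estimate | Mean SE | Coverage of true effect |
|---|---|---|---|
| Students, carried forward | 0.40 | 0.119 | 0.885 |
| Students, completers | 0.50 | 0.149 | 0.95 |
| Teachers, carried forward | 0.56 | 0.166 | 0.876 |
| Teachers, completers | 0.70 | 0.204 | 0.95 |

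Adding a common decline of 0.5 SD with equal drop-out leaves the student estimate at 0.40 and coverage at 0.887. The interval is narrower than the completers' interval and is centred 0.10 SD away from the truth.

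**4. Unequal drop-out with a common decline (τ = −0.5, assumed).**

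- δ = 0, 10% intervention vs 30% control: 0.9 × (−0.5) − 0.7 × (−0.5) = −0.10. Simulated false rejections are about 11–12%, against 5% for completers.
- δ = 0, 15% vs 25%: 0.85 × (−0.5) − 0.75 × (−0.5) = −0.05.
- δ = −0.50, 10% vs 30%: 0.9 × (−1.0) − 0.7 × (−0.5) = −0.55, an exaggeration.
- δ = −0.50, 30% vs 10%: 0.7 × (−1.0) − 0.9 × (−0.5) = −0.25, half the true reduction. Coverage is about 0.56.

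**5. Power of the primary test, equal drop-out, 720 students.** The zeros reduce the spread as well as the mean.

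- Total variance of change, averaged over arms: 0.8 + 0.8 × 0.2 × 0.25/2 = 0.82.
- Between-school part: 0.64 × 0.05 = 0.032.
- Intra-cluster correlation: 0.032/0.82 = 0.039. Design effect: 1 + 59 × 0.039 = 3.30.
- SE carried forward: √(2 × 0.82 × 3.30/360) = 0.123, so effect/SE = 0.40/0.123 = 3.26.
- SE completers: √(2 × 3.35/288) = 0.153, so effect/SE = 0.50/0.153 = 3.28.

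Noncentral t power on 10 df is 0.836 against 0.839; simulation gives 0.84 for both. For teachers it is 0.84 against 0.85.

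**The case against.** The best defence is that the rule keeps every randomised participant in the analysis, is fixed in advance, pulls the estimate towards no effect and costs no power. The power part stands. A reader might infer that the diluted effect takes power below the stated 0.80. A figure of 0.77 does appear if the intra-cluster correlation is held at 0.05 with 60 per school (design effect 3.95), but that ignores the shrinkage of between-school variance in step 5. The 0.80 also refers to 430 students and 104 teachers, not to the planned 720 and 180. Conservatism holds only when drop-out is similar in both arms; step 4 shows movement away from zero as well as towards it.

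A reader might also infer that drop-out here depends on the outcome, because the Background lists "poor academic performance, and increased school drop-out rates and absenteeism" among the consequences of school violence. That is general literature on leaving school, not a statement about loss from this trial over three months. The dependence is possible but not documented, and if strong it would trouble a missing-at-random model too.

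Nor does the use of 48 per school in the sample size and 60 in the analysis amount to a material conflict: the design effects are 3.35 and 3.30.

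Finally, sensitivity analyses and drop-out tables may be in a full plan that is not shown, so their absence is no fault. The carry-forward rule itself, however, is stated here.

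**Conclusion.** The concern holds as one of bias and interval coverage. The no-change assumption is explicit, governs the primary analysis and is not supported by the attrition the protocol expects. With 20% drop-out in both arms, and drop-outs who would otherwise change like completers, the student effect is understated by one fifth (0.50 to 0.40 SD) and 95% intervals cover about 88–89% of the time. With unequal drop-out and a common trend, both assumed, the error can take either sign and can raise the false-positive rate to about 11–12%. The size in this trial cannot be known beforehand, since it depends on arm-specific drop-out and drift that the documents do not give. With equal drop-out, no material loss of power in the primary time × group test is shown. The matter should be corrected before analysis.

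**What to change.** Replace the carry-forward sentence under Analysis. Either of these would serve as the primary analysis:

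- a likelihood-based mixed model with a school effect, fitted to all observed data and conditioning on the baseline score; or
- multilevel multiple imputation using arm, school, baseline Conflict Tactics Scale score, sex and school year for students, with the corresponding variables for teachers.

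Keep carrying forward only as a sensitivity analysis, beside one in which the drop-outs' imputed values are shifted by stated amounts.

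The cost is a change of wording and slightly more programming; no new data are needed. The downside is reliance on data being missing at random given the variables in the model. This cannot be verified from the data, which is why the shifted imputation is included.

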## Methods/design

### Study design

In a two-arm cluster randomized controlled trial, 12 secondary schools will be randomly assigned to the intervention group (which will receive the ICC-T intervention training) or the control group (which will receive no training). The study will have two data collection points: pre-assessment and follow-up assessment. See Figs. 1 and 2 and the Standard Protocol Items: Recommendations for Interventional Trials (SPIRIT) checklist (Additional file 1).

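### The main test compares change scores, and the two supporting t tests lack a control arm or ignore baseline and schools; one baseline-adjusted, cluster-aware comparison would usually serve better

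*Protocol article*

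**What the plan says.** The Study design section fixes two assessments: "The study will have two data collection points: pre-assessment and follow-up assessment". The Analysis section names, as the main analysis of students' exposure to and teachers' use of violence, the time × group "interaction effects using repeated multivariate analysis of variance (MANOVA").

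It then sets the order of testing: "Multivariate interaction effects and the univariate interaction effect of each outcome variable will be tested first". Two further tests follow:

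- a paired t "test analysis will examine the differences from the pre-assessment to follow-up assessment in the intervention group";
- an independent t "test will examine whether there is a difference between the control group and intervention group at the follow-up assessment".

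Cohen's d benchmarks are given for interpreting the t tests. No baseline-adjusted comparison between arms is specified. Schools enter the model only on a condition: "In case of a noted cluster effect (intra-cluster correlation coefficient > .10) we shall use multilevel analysis". The Participants section plans with an ICC of 0.05, below that threshold.

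**The concern.** With two time points, the univariate time × group interaction is the two-sample test on follow-up minus baseline. That forces the coefficient of the baseline to be 1, whereas regression on baseline estimates it from the data. When the pre-post correlation is modest, subtracting the whole baseline adds noise, and precision is lost on data that will already have been collected.

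The two supporting tests have different faults. A before-after test in one arm cannot separate ICC-T from time, retest or regression to the mean. The follow-up t test leaves out the baseline and, at an ICC of .10 or less, treats students and teachers as independent of their school. It also gives a second between-arm answer that may disagree with the interaction.

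**Working it through.** **Inputs from the article.** Students: f = 0.25 (d = 0.5), 60 per school, 20% drop-out, so 48 per school, ICC 0.05. Teachers: f = 0.35, 15 per school, so 12 after drop-out, ICC 0.05. Six schools per arm. Pre-post correlations are not given. Those below are assumptions.

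**The plan's own figures.** A two-group F test with noncentrality N·f² needs N = 128 at f = 0.25 (power 0.801) and N = 67 at f = 0.35 (power 0.806). Students: DE = 1 + 47 × 0.05 = 3.35, and 128 × 3.35 = 428.8 (stated 430). Teachers: DE = 1 + 11 × 0.05 = 1.55, and 67 × 1.55 = 103.9 (stated 104). Both reproduce without any pre-post correlation.

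**Precision, one common correlation r.** In units of the outcome variance, the change score has variance 2(1 − r) and the baseline-adjusted score 1 − r². The ratio is (1 + r)/2, so the saving is (1 − r)/2.

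| r | ratio | saving |
|---|---|---|
| .3 | .65 | 35% |
| .5 | .75 | 25% |
| .7 | .85 | 15% |

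**Effect of carrying observations forward.** With 20% of participants assigned no change (and otherwise like the rest), the analysed correlation is about .8r + .2. So .3 becomes .44 (saving 28%), .5 becomes .60 (20%) and .7 becomes .76 (12%).

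**Different correlations at the two levels.** Let rᵢ be the within-school correlation and rₛ the school-level one. Arm is a school-level factor, so school means matter. Put b = .05, w = .95/48 = .0198 and V = b + w = .0698. The variances of a school mean are:

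- change score: 2(1 − rₛ)b + 2(1 − rᵢ)w;
- adjusted for own baseline only (slope close to rᵢ): b(1 + rᵢ² − 2rᵢrₛ) + w(1 − rᵢ²);
- adjusted also for the observed school-mean baseline: V − (b·rₛ + w·rᵢ)²/V.

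For rᵢ = .3 and rₛ = .8 these are .0477, .0485 and .0396.

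| rᵢ / rₛ | own baseline only ÷ change score | own + school mean ÷ change score |
|---|---|---|
| .3 / .8 | 1.02 | .83 |
| .3 / .9 | 1.21 | .87 |
| .5 / .9 | 1.09 | .89 |

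The last column treats the school-level slope as known. Estimating it from 12 schools multiplies the variance on average by 1 + 1/(10 − 2) = 1.125 under normality. The three ratios become about .93, .97 and 1.00. In the common-correlation cases, .65, .75 and .85 become .73, .84 and .96.

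**Paired t test.** Suppose no intervention effect but a drift of 0.1 SD in both arms. With 6 × 48 = 288 intervention students, the standard error is √(2(1 − r)/288), which is .070, .059 and .046 at r = .3, .5 and .7. The chance of p < .05 is then 30%, 40% and 59%, before any effect of clustering.

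**Follow-up t test at ICC .05.** Type I error ≈ 2[1 − Φ(1.96/√DE)]. Students: 1.96/√3.35 = 1.07, giving 28%. Teachers: 1.96/√1.55 = 1.57, giving 12%.

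**The case against.** The strongest reply is that the main test is sound in principle. The interaction is a randomised between-arm contrast, it already uses the baseline, and it is tested first. Preferring change scores costs efficiency and adds no bias. This stands. The same ICC rule does leave the interaction's standard error at individual level, but that is a separate defect and no argument for adjustment over change scores.

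The second reply is that the size of the gain is unknown. This also stands: the school-level correlation is not in the article, and an own-baseline-only model can be worse than the planned contrast.

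Several stronger inferences are tempting but unsupported:

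- The article reports: "The scale has acceptable internal consistency for physical violence (α = .55) and emotional violence (α = .69) in previous studies". These are internal consistencies, not retest values, and do not show a low pre-post correlation.
- Reading f = 0.25 on the outcome SD would raise 128 to 128 × 2(1 − .3) ≈ 179 at r = .3. The article ties f to interaction effects. If f is on the change-score scale, 128 holds for any r.
- Power gains from a 10-df school-level test do not describe the individual-level test planned at ICC .05. They would in any case depend on both correlations.
- The article does not say whether the t tests stay at individual level once multilevel analysis is triggered, nor that they will be presented as proof of efficacy.

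**Conclusion.** The point holds as a worthwhile improvement to the main analysis and as a real fault in the two t tests. It does not show that the main analysis is invalid.

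The loss from change scores is 15% to 35% of variance for a common r from .7 to .3, or 12% to 28% after carrying observations forward. Both ranges precede the cost of estimating a school-level slope. Where schools are far more stable than individuals, the gain over change scores is small or absent, even with the school-mean baseline included. A reader might infer that precision is certainly being wasted; without both correlations the article cannot support that.

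The faults in the t tests do not depend on whether adjustment beats change scores. The paired test has no control at any correlation. The follow-up test needs no baseline adjustment to be unbiased, but its nominal 5% is about 28% for students and 12% for teachers at the protocol's own ICC, by normal approximation with 48 and 12 per school.

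**What to change.** For each primary outcome, make the main estimate the between-arm difference at follow-up from a mixed model with a random school intercept. Adjust it for the participant's own baseline score and the school-mean baseline score, and use small-sample degrees of freedom. Fit it whatever the observed ICC. Replace the independent t test with this adjusted difference and its 95% confidence interval. Show within-arm change descriptively, without a p value. If power is quoted, state it as conditional on assumed individual-level and school-level correlations.

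No new data are needed, since baseline is already scheduled; only the analysis text changes. The statistical cost is one school-level degree of freedom (12 − 2 = 10 becomes 9), together with the uncertainty of a slope estimated from 12 school means.
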